## Abstract

**Background:**

In the UK, Black African-Caribbeans (ACs) and South Asians (SAs) have 3–6 times greater risks of developing type-2 diabetes mellitus (T2DM) and significantly higher prevalence of vitamin D (vitD) deficiency than White Caucasians. East London is among the areas with the highest prevalence of T2DM and the highest proportion of ethnic minority groups. This ethnic health inequality is ascribed to socioeconomic standing, dietary habits, culture, and attitudes, while biological diversity has rarely been investigated.

**Aim:**

The study aims to investigate the difference in the postprandial glycemic response (PGR), an independent risk factor of T2DM, between ethnic groups (White Caucasians, SAs, and ACs) in East London and its association with vitD status.

**Methods:**

This acute randomized crossover trial will recruit healthy adults (n = 106) in East London between November 2023 and March 2025. Two test drinks are consumed by participants (a glucose drink containing 75 g glucose and pure orange juice) on different occasions. PGRs are monitored before and after drinking every 30 min for up to 2 h via finger prick. A fasting blood sample obtained via phlebotomy will be used for plasma 25(OH)D and relevant tests. A knowledge/perception questionnaire about vitD and a 4-day food diary (analyzing vitD dietary intake) will also be collected. Data will be analyzed using a multiple linear regression model adjusted by confounding factors (age, gender, body mass index, and body fat percentage).

**Summary:**

The study results will be disseminated through journals and conferences, and target stakeholders.

## Introduction

Health patterns differ significantly between ethnic minority groups and the White population. In the UK, the risk of developing type 2 diabetes mellitus (T2DM) is 3–6 times greater in South Asians (SAs) and up to three times greater in Black African-Caribbeans (ACs) than in White Caucasians, and people in these groups develop this condition at a younger age (Meeks et al., 2016). East London is among the areas with the highest proportion of ethnic minority groups (Gov.uk, 2022a) and the highest prevalence of T2DM (Diabetes, 2021). Although multiple factors, including socioeconomic standing, diet, culture and attitudes, language barriers, genetics, and lifestyles, have been identified (Hanif and Susarla, 2018), research into biological diversity is scarce. Recent research revealed that the postprandial glucose peak in SAs is 2–3 times greater than in White Caucasians after identical carbohydrate loads are reached (Tan et al., 2017). Although obesity is believed to account for 90% of the risk of developing T2DM due to obesity causing insulin resistance (Grant et al., 2021) and some ethnic minority groups, e.g. Black people, have a higher prevalence of overweight and obesity than White British people do (73.6% vs. 63.3%) (Gov.uk, 2020), other biological mechanisms, including vitamin D (vitD) deficiency, are poorly understood.

VitD deficiency in ethnic minorities in the UK is well known and is described as an unrecognized epidemic (Darling, 2020). In the UK, 50% of SAs and 33% of Black ACs demonstrate vitD deficiency, whereas 17.5% of White Caucasians do (Sutherland et al., 2021), which is primarily due to more subcutaneous pigmentation that absorbs ultraviolet B from sunlight and reduces vitD production in the skin and at high latitudes in the UK (Yousef et al., 2023). This situation is worse in East London. In Tower Hamlets, a borough of East London, 80–97% of the residents are thought to have vitD deficiency, significantly higher than the national population at 50% (Towerhamlets.gov.uk, 2017). An inverse association of serum 25(OH)D levels with insulin resistance was observed in healthy adults (Yin et al., 2022) and diabetic patients (Abubaker et al., 2022). Recent evidence from systematic reviews and meta-analyses of randomized controlled trials (RCTs) suggests that vitD supplementation may help reduce fasting plasma glucose concentrations, HbA1c levels, and insulin resistance in patients with T2DM (Afraie et al., 2024; Farahmand et al., 2023). However, little evidence is available that focuses on ethnic minority groups or residents in East London, indicating that AC and SA communities are underrepresented in the evidence base concerning diabetes and vitD.

VitD plays an important role in calcium metabolism and is involved in the modulation of cell growth, neuromuscular and immune function, and the reduction of inflammation due to its receptors being expressed ubiquitously in nearly all human cells, including pancreatic β-cells (Lips et al., 2017). Animal studies have shown that vitD treatment improves insulin production and sensitivity via decreasing inflammatory response and regulating glucose homeostasis (Zhang et al., 2024), or via increasing intracellular calcium in pancreatic ß-cells and other metabolic pathways (Szymczak-Pajor et al., 2020). Moreover, 1,25(OH)_2_D (the active form of vitD) may modulate β-cell growth and differentiation (Lips et al., 2017). The secondary high parathyroid hormone (PTH) concentration (Malik et al., 2020) and increased inflammatory markers (Zhou and Hyppönen, 2023) associated with vitD deficiency may also cause glucose intolerance. VitD may have an indirect effect on glycemic control via obesity. Previous evidence (Rafiq and Jeppesen, 2018) revealed a significant inverse association between body mass index (BMI) and serum 25(OH)D, which is thought to involve a complex of mutual influences because vitD receptors are expressed on adipose cells and regulate their functions (Bennour et al., 2022), indicating that vitD deficiency might be one of the causes of obesity, thus indirectly leading to an increased risk of T2DM.

The postprandial glycemic response (PGR) has important implications for the development of T2DM (Shibib et al., 2024). The oral glucose tolerance test (OGTT) is widely used to assess insulin sensitivity and pancreatic β-cell function and to assess an individual's metabolic capacity to handle carbohydrate-containing foods (American Diabetes Association, 2013). However, a recently published study indicated that within-subject variations in the PGR pattern may exist between OGTT and food intake, suggesting the necessity of combining OGTT and a meal/drink tolerance test for individualized glycemic management (Liu et al., 2022). There is poor awareness about vitD and its impact on health in the UK. Although the COVID-19 pandemic has brought increased public attention to vitD, only around one in six individuals in the UK have been reported to take a daily vitD supplement (Gov.uk, 2022b). However, no such data is currently available for ethnic minority groups or residents of East London. We are also interested in dietary vitD intake between different ethnic groups in East London, which will partly explain the vitD status of the target population.

Overall, the evidence on the association of vitD and the risk factors of T2DM in the ethnic minority groups is scant. There is an urgent call for research on ethnic minority populations to address health inequality (The NHS Race and Health Observatory, 2021). This proposal aims to respond to the above call by focusing on ethnic minority communities in East London via investigating the association between vitD status and PGRs among White Caucasian, SA, and AC adults. The objectives of the study include (1) investigating PGRs to an OGTT, as well as to the consumption of a commonly consumed drink, pure orange juice (OJ); (2) measuring parameters in the blood including 25(OH)D (an indicator of vitD status), and other relevant tests including calcium, parathyroid hormone (PTH), blood lipid profile, inflammatory parameters; (3) assessing the knowledge and perception of vitD; (4) evaluating the dietary vitD intake, in White Caucasian, SA and AC adults.

## Method

This is an acute, randomized, repeated measures crossover trial. Figure 1 shows the study flow chart. The proposal was approved by the Senate Research Ethics Committee at City St George's, University of London (Ref ETH2223-2000). This study was registered with ClinicalTrials.gov (identifier: NCT06241976). The recruitment period of the study is between 1 November 2023 and 31 March 2025 in London, UK. The informed consent is obtained from all participants before taking part in the study.

**Figure 1. fig1-02601060251356528:**
[figure not shown]
Study flow diagram.

Study status: A) participant recruitment will be completed at the end of March 2025; B) data collection will be completed at the end of March 2025; C) results are expected in April and May 2025. None of these stages have already been completed when the manuscript was submitted.

## Participants

The inclusion criteria are as follows: 18–65 years in general good health and living in East London from White, SA or Black AC origins. The exclusion criteria are as follows: diabetes; digestive system diseases; BMI < 18.5 kg/m^2^; liver or kidney disease; other chronic diseases; blood clotting disorders; alcohol consumption (>14 units per week); regular smoking (one or more cigarettes per day); pregnancy; maternity; and mixed race. A self-developed health and lifestyle questionnaire (Appendix 1) will be used to screen the eligibility of the participants. Participants will provide informed consent online before being screened for eligibility.

## Recruitment

There are a few methods of recruiting participants. We will recruit staff and students who live in East London with gatekeeper permissions from the Dean of the school. Recruitment adverts will be circulated to staff and students at City St George's, University of London. There are 19975 students, among whom 64% are from the UK, and a large proportion of students are from different London boroughs, including the East London area. Each year, many staff and student projects recruit participants successfully in this way. In addition, we recruit participants from local communities in East London with gatekeeper permission. We will contact local ethnic communities, including the Bangladeshi Community, London Central Mosque, Bangladesh Embassy and Indian & Bangladesh Hindu Community East London, etc. We will also recruit participants via social media, including Meta (formerly Facebook), X (formerly Twitter), Instagram, and LinkedIn. To encourage taking part in the study, participants will receive a shopping voucher worth £20 per visit as a gesture of thanks and an incentive.

## Study design

The participants will consume a glucose drink (75 g glucose in 300 ml water, 281 kcal) used for the OGTT (Eyth et al., 2023) and pure OJ (Tesco 100% Pure Squeezed Orange Juice Smooth 300 ml containing 129 kcal, 30 g sugar, 0.3 g fiber, 1.8 g protein and 90 mg vitamin C) on separate occasions with at least 48-h interval and at random order. The two drinks were chosen rather than meals because of fewer facilities needed to cater to participants, fewer potential food hygiene issues, and being more acceptable to participants from different ethnic backgrounds. The participants fast for 8–12 h. The blood glucose concentration is measured via a HemoCue Glucose 201+ Analyzer (Health-care Equipment & Supplies, Surrey, UK) at 0, 30, 60, 90, and 120 min before and after drink consumption by finger prick. Seven milliliters of fasting blood will be collected via phlebotomy on the first visit. If blood collection is unsuccessful on the first visit, it will be attempted on the second visit. The plasma is separated by centrifuging the blood sample at 2000 × g for 10 min and stored at −20°C until analysis of the metabolic parameters (refer to the section on outcome measures).

Participants are asked to consume the drinks (either a glucose drink or OJ) within 5 min in the resting area outside the clinic room. The researcher will record the start and end times of consumption. During the 2-h study period, the participants are asked to remain sedentary and refrain from eating or drinking while sitting in the resting area. On the evening before each study visit, participants are encouraged to consume similar meals across both visits, ensure adequate sleep, and avoid alcohol consumption and strenuous physical activity. On the study visit, the researcher will collect information on the participant's dinner from the previous evening, hours of sleep, alcohol intake, and physical activity.

The name, email/mobile (for appointment purposes), sex, age, and ethnicity of the participants are also collected. The research assistant (ST) will generate the allocation sequence, enroll participants, collect consent forms, assign participants to interventions and conduct the trial. The study is not blind to the researcher and participants but is blind to the statistician (SI) who will analyze the data.

## Randomization

The order of drink consumption is randomized by using the Excel RAND function. In an Excel spreadsheet, a list of participant numbers is shown in one column. In the next column, we use the RANDBETWEEN function and choose 0 and 1 as the ranges to randomly generate values of 0 or 1. Participants with a value of 0 will consume a glucose drink first, while participants with a value of 1 will consume pure OJ as their first drink.

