## Data analysis

The sample size was calculated using G*Power software (version 3.1.9.7; Heinrich Heine University, Düsseldorf, Germany), based on F-tests for ANOVA: repeated measures, between-subjects factors. This study aims to achieve an effect size of 0.25 in the PGRs among three ethnic groups, considering that the response is taken from five different time points with 30-min intervals for each person, and to achieve 80% power in the study, we will need 32 people in each group (n = 96 in total) at the 5% level of significance. The details of the sample size calculation can be found in Appendix 3. Considering the acute nature of the study, we believe 10% of the attention is sufficient; therefore, the target number of recruitments is 106 participants. Data normality will be assessed using the Kolmogorov–Smirnov test. Continuous variables with a normal distribution will be presented as means ± standard deviations, while non-normally distributed data will be reported as medians and interquartile ranges. Categorical data are presented as numbers and percentages. The iAUC is calculated using approximated trapezoidal numerical integration (Chlup et al., 2008), and only the incremental area above the fasting level will be included. The association of plasma 25(OH)D concentrations and the iAUCs and PVs, respectively, will be analyzed using a multiple linear regression model adjusted by age, gender (using dummy variables), BMI, and body fat percentages, including all participants, as well as in different ethnic groups. The iAUCs and PVs concentrations between ethnic groups after each drink consumption will be analyzed by one-way ANCOVA adjusted by confounding factors including fasting glucose concentration, age, sex, BMI, and body fat percentage. The correlation of iAUCs and PVs between the two drink consumptions is analyzed by Pearson's correlation to identify the difference in the pattern of PGRs to different drink consumptions. Other continuous variables (e.g. plasma 25(OH)D etc.) between ethnic groups will be analyzed by one-way ANCOVA adjusting confounding factors (age, gender, BMI and body fat percentage). Categorical variables, e.g. gender, the percentage of patients with vitD deficiency etc., are compared between ethnic groups via Chi-square tests. The statistical significance will be reported with a *P*-value (significance was set at *P* ≤ 0.05, two-tailed) and a 95% confidence interval. The statistical software IBM SPSS 29 will be used to analyze the data. The percentage of missing data is expected to be low based on our previous experience. Therefore, regression imputation is used to address missing data. Both intention-to-treat analysis and per-protocol analysis will be used for the data analysis.

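### Drink order is randomised without balance by ethnic group and appears in neither stated model, so a chance imbalance in order can shift the between-person ethnic comparisons slightly; adding order as a factor removes this at almost no cost.

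*Protocol article*

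**What the plan says.** **Allocation (Protocol article, Randomization).** Participant numbers stand in one spreadsheet column, and in the next "we use the RANDBETWEEN function and choose 0 and 1 as the ranges to randomly generate values of 0 or 1". One value means the glucose drink first, the other means orange juice first. No blocks and no strata by ethnic group are described. The section opens by naming the RAND function and then describes RANDBETWEEN.

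**Roles and visits (Study design).** One research assistant "will generate the allocation sequence, enroll participants, collect consent forms, assign participants to interventions and conduct the trial". Researcher and participants are not blinded; the statistician is. On the visits: "Seven milliliters of fasting blood will be collected via phlebotomy on the first visit". It moves to the second visit only if the first attempt fails. The visits are at least 48 hours apart.

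**Models (Data analysis).** The iAUCs and PVs "between ethnic groups after each drink consumption will be analyzed by one-way ANCOVA", with fasting glucose, age, sex, BMI and body fat as covariates. The regression of iAUC and PV on 25(OH)D, which carries the primary outcome, adjusts for age, gender, BMI and body fat. Drink order or visit number is in neither list.

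**The concern.** In a crossover analysed within person, a visit effect can be separated from the drink effect or largely cancels. Here the main contrasts are between people: for each drink, ethnic groups are compared on values that come from visit 1 for some participants and visit 2 for others. If visit affects the glucose response (first exposure to the procedure, or venepuncture on the same morning), and one ethnic group happens to take that drink at visit 1 more often than another, part of the visit effect appears as an ethnic difference.

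The 25(OH)D regression is exposed in the same way wherever order happens to be associated with 25(OH)D. The only factor the trial randomises is thus absent from both stated models. The ethnic contrasts are secondary outcomes, but the sample size is built on them.

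**Working it through.** **1. The plan's own figure.** Inputs from Data analysis: "This study aims to achieve an effect size of 0.25 in the PGRs among three ethnic groups"; "the response is taken from five different time points with 30-min intervals for each person"; "to achieve 80% power in the study"; "at the 5% level of significance". The correlation between time points is not in the article (details are referred to Appendix 3), so 0.5 is assumed. For a repeated-measures F-test of a between-subject factor:

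λ = N·f²·m / (1 + (m − 1)ρ) = 96 × 0.0625 × 5 / (1 + 4 × 0.5) = 30 / 3 = 10, with 2 and 93 degrees of freedom. Power = 0.802.

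So 96 (32 per group) reproduces, and 96 × 1.10 = 105.6 rounds to the stated 106. The steps below use 32 per group.

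**2. How uneven can order be between ethnic groups?** Under the described draw, the number taking a given drink first in each group is Binomial(32, 0.5), independent across groups. Exact enumeration over three groups gives:

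| Event | Probability |
|---|---|
| Some pair differs by ≥ 20 percentage points | 23% |
| Some pair differs by ≥ 25 percentage points (8 or more people of 32) | 14% |
| One group at 20:12 or beyond and another at 12:20 or beyond | 6% |

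The expected largest gap between any two groups is 15 percentage points.

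**3. What does a gap do to a contrast?** Shift = gap in share × visit effect. The documents give no visit effect, so the values below are assumptions. For a gap of 20/32 − 12/32 = 0.25:

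| Assumed visit effect (SD) | Shift in contrast (SD) |
|---|---|
| 0.1 | 0.025 |
| 0.2 | 0.05 |
| 0.3 | 0.075 |
| 0.5 | 0.125 |

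The standard error of a pairwise contrast, before covariates, is √(2/32) = 0.25 SD. At 0.3 SD the shift is therefore 0.075/0.25 = 0.3 standard errors.

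**4. Type I error of the three-group F-test** (simulation, 40,000 runs per cell, no true ethnic difference, other covariates left out):

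| Allocation and model | Visit effect 0.2 SD | Visit effect 0.5 SD |
|---|---|---|
| Coin-flip order, order not modelled | 5.0% | 5.0% |
| Shares fixed at 12/16/20 of 32, order not modelled | 5.1% | 6.0% |
| Order balanced within group, order not modelled | 4.6% | 4.2% |
| Coin-flip order, order modelled | 5.0% | 5.0% |
| Shares fixed at 12/16/20, order modelled | 5.0% | 5.1% |

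**5. Price of the order term.** One error degree of freedom, plus a small loss when order is uneven. With shares 12/16/20, the within-group sum of squares of order is 12×20/32 + 16×16/32 + 20×12/32 = 7.5 + 8 + 7.5 = 23. The squared standard error of the extreme contrast becomes 2/32 + 0.25²/23 = 0.0625 + 0.0027 = 0.0652. The standard error is then 0.255 SD instead of 0.25.

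**The case against.** The strongest reply is that randomisation already deals with this. An honest coin flip is independent of ethnicity, so there is no systematic bias, and the unadjusted test has its nominal error rate averaged over allocations. This stands. A reader might infer that the omission inflates false positives in general; step 4 shows that it does not. The harm is conditional on an uneven realised list, and even then it is small. The variance left unexplained is also small: a 0.3 SD effect at an even split contributes 0.25 × 0.09 = 0.0225 to a variance of about 1, roughly 2%.

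A reader might also judge the risk by how often a single group splits unevenly. That is much commoner than a gap between groups, but it is the gap that shifts a contrast, so 14% (or 6% for opposite splits) is the relevant figure.

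A further tempting inference is that the list was left live, redrawing with each recalculation, and was unconcealed. The article does not say so. It describes neither fixing nor concealment, and silence in a condensed article is not evidence of a fault. What it does state is that one unblinded person generates, enrols and assigns. That would permit order to be steered by ethnicity, but nothing suggests it happened. Everyone takes both drinks, glucose is read by an analyser and the statistician is blinded, so concealment matters less than in a parallel-group trial.

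Existing features help in part: iAUC counts only area above the fasting level, the ANCOVA adjusts for fasting glucose, and similar evening meals are encouraged. None of them addresses a visit effect on the response after the drink. The article says the ANCOVA is run for each drink, but does not say how the regression handles the two drinks, so the point is firmest for the ANCOVA.

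**Conclusion.** The point holds as a modest, nearly free improvement. Order is drawn without described balance by ethnic group, the ethnic comparisons are between people for each drink, the visits differ by design, and neither stated covariate set contains order. The consequence is limited to chance imbalance: a 14% chance of a gap of 25 points or more between some pair of groups, and at a 25-point gap a shift of 0.075 SD (0.025 to 0.125), about 0.3 standard errors (0.1 to 0.5). This rests on 32 evaluable people per group, independent fair draws, and an assumed visit effect of 0.3 SD (0.1 to 0.5) that is common to all groups. The documents do not support a claim of systematic bias, of a list left live, or of order being steered.

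**What to change.** **Main change.** Add drink order (for a given drink, the same thing as the visit at which it was taken) as a two-level factor in each iAUC and PV ANCOVA and in each regression of iAUC or PV on 25(OH)D. This costs one degree of freedom per model and needs no new data, since the order is known for everyone. It works whatever list was realised. Balancing alone would not replace it: step 4 shows that balanced but unmodelled order makes the test slightly conservative.

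**Secondary, only for participants not yet allocated.** Use a list balanced within ethnic group (for example, permuted blocks by group), saved as fixed values and held by an existing team member who does not enrol. With recruitment closing at the end of March 2025, this may affect few participants or none. It needs no added staff.

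**Wording.** State which spreadsheet function was used, since the Randomization section names two, and say whether the draws were fixed before use and who held the list.
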